## Abstract

**Introduction:**

Long COVID (LC), also known as post-COVID-19 syndrome, refers to symptoms persisting 12 weeks after COVID-19 infection. It affects up to one in seven people contracting the illness and causes a wide range of symptoms, including fatigue, breathlessness, palpitations, dizziness, pain and brain fog. Many of these symptoms can be linked to dysautonomia or dysregulation of the autonomic nervous system after SARS-CoV2 infection. This study aims to test the feasibility and estimate the efficacy, of the heart rate variability biofeedback (HRV-B) technique via a standardised slow diaphragmatic breathing programme in individuals with LC.

**Methods and analysis:**

30 adult LC patients with symptoms of palpitations or dizziness and an abnormal NASA Lean Test will be selected from a specialist Long COVID rehabilitation service. They will undergo a 4-week HRV-B intervention using a Polar chest strap device linked to the Elite HRV phone application while undertaking the breathing exercise technique for two 10 min periods everyday for at least 5 days a week. Quantitative data will be gathered during the study period using: HRV data from the chest strap and wrist-worn Fitbit, the modified COVID-19 Yorkshire Rehabilitation Scale, Composite Autonomic Symptom Score, WHO Disability Assessment Schedule and EQ-5D-5L health-related quality of life measures. Qualitative feedback on user experience and feasibility of using the technology in a home setting will also be gathered. Standard statistical tests for correlation and significant difference will be used to analyse the quantitate data.

**Ethics and dissemination:**

The study has received ethical approval from Health Research Authority (HRA) Leicester South Research Ethics Committee (21/EM/0271). Dissemination plans include academic and lay publications.

**Trial registration number:**

NCT05228665.

STRENGTHS AND LIMITATIONS OF THIS STUDYTo our knowledge, this is the first study of heart rate variability biofeedback (HRV-B) in long COVID and will provide new information regarding the feasibility of the technology-based intervention in this condition.The estimation of efficacy will determine the scope and sample size for a larger controlled trial in the condition that currently has no definitive treatments.The study will provide preliminary evidence on the correlation between long COVID symptoms and dysautonomia.The limitation of this study is the small sample size of 30 participants, which might not give an accurate estimate of efficacy.HRV-B is a technology-based intervention; therefore, its take-up could be limited in those with a lack of experience in using digital technology in daily life, particularly those from less privileged backgrounds.

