### Aims and objectives

The aim of this study is: to assess the feasibility of a 4-week HRV-B-structured breathing programme in individuals with LC.

The objectives include:

Does breathing exercises through HRV-B increase HRV among participants with LC?Are consumer-grade monitors appropriate technology to use for HRV-B in the domiciliary setting?Does regular HRV-B have any effect on LC symptoms?

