## Methods

### Study design

This is a phase 2 uncontrolled open-label feasibility study of a home technology-based HRV-B in 30 individuals with LC. Potential participants will be identified through the Leeds COVID-19 Rehabilitation Service, based at Leeds Community Healthcare NHS Trust. The study period will be 6 weeks for each participant. The study start date is 24 January 2022, and the anticipated end date is 31 March 2024.

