## Sample size

A formal sample size calculation is not required for a feasibility study as it does not mimic a definitive randomised trial and aim is not to measure effect size.^35^ A sample size of 30 is the average sample size across feasibility studies and is accepted as reasonable size to assess the acceptability and suitability of the intervention.^36^

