## Statistical analysis

Quantitative data from standardised questionnaires will be scored as per standard procedures. Data downloaded from the wearable devices will be extracted, cleaned and summarised using specific software packages, including Matlab and Python. Quantitative data will be analysed with simple descriptive statistics. The presence and magnitude of pre and postintervention differences will be examined using repeated paired sample t tests (with Bonferroni adjustment for multiple comparisons), and the effect size will be explored using both Analysis of Variance (ANOVA) partial η^2^, and Cohen’s d. Additional exploratory analyses may also be performed to fully analyse the data set produced, guided by the findings of the descriptive statistics.

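### An uncontrolled pre/post effect size, disclaimed as an aim in the sample size section, is nevertheless meant to set the sample size of a later controlled trial, and is likely to overstate the effect that trial must detect

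*Protocol article*

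**What the plan says.** The Sample size section states that no formal calculation is needed because, among other reasons, the "aim is not to measure effect size". It then rests the number on convention: "A sample size of 30 is the average sample size across feasibility studies".

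Four other places in the article treat the effect as something to be estimated:

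- The abstract's introduction: "This study aims to test the feasibility and estimate the efficacy, of the heart rate variability biofeedback (HRV-B) technique".
- The strengths and limitations box: "The estimation of efficacy will determine the scope and sample size for a larger controlled trial".
- The closing paragraph of the introduction (under HRV biofeedback), which includes estimating the effect on symptoms among the things the authors wish to do.
- The Statistical analysis section, where pre/post differences are tested with paired t tests and "the effect size will be explored using both Analysis of Variance (ANOVA) partial" eta-squared and Cohen's d.

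Under Aims and objectives the formal aim is feasibility only, but the third objective asks: "Does regular HRV-B have any effect on LC symptoms". Under Study design: "This is a phase 2 uncontrolled open-label feasibility study of a home technology-based HRV-B in 30 individuals with LC". The only reason the box gives for a possibly inaccurate efficacy estimate is the sample of 30. The absence of a control group is not mentioned there.

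**The concern.** There are two linked problems. First, the reason for not justifying the sample size (effect size is not the aim) is contradicted by the use planned for the result (the effect estimate sizes the next trial). Second, that use does not work with this design. A controlled trial is sized on the difference between arms. A single-arm study yields only the change within patients, and the two are equal only if untreated patients would not change at all.

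The article itself gives reasons to expect some change without a specific treatment effect. The primary outcome is self-reported and unblinded. Researchers telephone every week. Entry depends on at least moderate palpitations or dizziness on the same scale that serves as primary outcome. Natural recovery over the six weeks is also possible.

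At stake is a later controlled trial planned on an inflated effect and so underpowered. A reader is also told that the weakness is imprecision, when a larger sample would leave this bias untouched.

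**Working it through.** **1. Inputs from the document.** One arm, open label, 30 participants; no alpha, power, target effect, SD or dropout. There is no calculation behind 30, so nothing can be reproduced. No effect size or sample size is given for the later trial.

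**2. Assumptions for illustration (mine, not the document's).** Observed pre/post d = 0.5, with 0.3 and 0.8 as a range. Later trial: two equal arms, two-sided alpha 0.05, 80% power, d inserted directly as the standardised difference between arms. Let s be the share of the observed change that a control arm would also show.

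**3. Precision at n = 30.** The 95% interval comes from the non-central t distribution with 29 degrees of freedom, with t = d × √30 (for d = 0.5, t = 2.74):

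- d = 0.3: −0.07 to 0.66
- d = 0.5: 0.12 to 0.88
- d = 0.8: 0.38 to 1.21

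Per-arm size is n = 2(1.96 + 0.8416)² / d² = 15.70 / d². At d = 0.5 this is 15.70 / 0.25 = 62.8, so 63. At the interval limits before rounding (0.116 and 0.876) it is about 1,165 and 21. This part is the imprecision that the article concedes.

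**4. Bias, which is not conceded.** The between-group effect is d(1 − s). Since n varies as 1/d², the required size is multiplied by 1/(1 − s)², whatever d is. For d = 0.5 and a trial planned at 63 per arm:

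| s | Effect between arms | Multiplier | Needed per arm | Power with 63 per arm |
|---|---|---|---|---|
| −25% (controls worsen) | 0.625 | 0.64 | 41 | 94% |
| 0 | 0.500 | 1 | 63 | 80% |
| 25% | 0.375 | 1.78 | 112 | 56% |
| 50% | 0.250 | 4 | 252 | 29% |
| 75% | 0.125 | 16 | 1,005 | 10% |

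The sample of 30 does not enter the multiplier. Recruiting more participants would narrow the interval in step 3 and leave this table unchanged.

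**5. Direction.** The document gives no value for s. The features pointing to s above zero are unblinded self-report (Study design, Outcome measures), weekly telephone reviews (Pre-HRV-B phase) and entry on items of the primary scale (Eligibility criteria), together with possible natural recovery. These make overstatement likely. They do not establish it.

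**The case against.** The strongest defence is that the sizing statement is a single forward-looking bullet. It gives no formula and does not say that the Cohen's d of the Statistical analysis section will be inserted anywhere. That section only explores effect size, the formal aim is feasibility, and the study is openly called uncontrolled. This is fair as to tone, but the bullet still says that the efficacy estimate will determine the later sample size, and within-patient change is the only such estimate this study can produce.

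Regression to the mean can also be overstated, and this stands in part. Entry uses palpitations or dizziness items only, whereas the scale also yields scores for functional disability, other symptoms and overall health. Baseline is taken at the first appointment, after screening, a week passes before the breathing programme starts, and the scale is completed seven times. These features reduce the bias without removing it, and they do nothing about response to unblinded treatment and contact.

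Two stronger readings are tempting and are not supported:

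- A reader might infer that the next trial would certainly be too small. That needs a positive background change, which the document does not quantify. At s = 0 there is no error, and if controls would worsen the trial is oversized.
- A reader might infer that a paired d is on the wrong scale and by itself inflates the effect. The article does not name the standardiser of Cohen's d, so the premise is not on the page. Even if the SD of change were used, the direction depends on the later analysis and the pre/post correlation r. The required size relative to plan is 1 for change scores, (1 + r)/2 (never above 1) for baseline-adjusted analysis, and 1/(2(1 − r)) for follow-up scores alone, which is 2.5 at r = 0.8, 1 at r = 0.5 and 0.71 at r = 0.3.

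**Conclusion.** The point holds in this form. The article contradicts itself on whether effect size is an aim, and it assigns to a single-arm pre/post estimate a task that only a between-group estimate can do. Overstatement of the effect, and so undersizing of the later trial, is likely but not certain, and its size is unknown. The multipliers of about 1.8, 4 and 16 hold for assumed background shares of 25%, 50% and 75% and do not depend on the assumed d. The per-arm numbers and power values additionally assume d = 0.5, alpha 0.05 and 80% power. The stated limitation is incomplete, because it names imprecision and omits the lack of a control.

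The convention-based choice of 30 is not itself shown to be wrong for a feasibility study. Nor does the document commit its authors to a causal reading of the third objective; the wording merely invites one.

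**What to change.** - Remove the statement in the strengths and limitations box that the efficacy estimate will set the later trial's scope and sample size.
- Make the abstract, the box, the introduction, the third objective, the Sample size section and the Statistical analysis section agree that pre/post change is descriptive. The third objective can ask about change in symptoms during HRV-B rather than the effect of HRV-B.
- Name the absence of a control group as a limitation beside the small sample.
- Report mean change in raw points with a 95% confidence interval. Cohen's d and partial eta-squared may stay if labelled descriptive and if the standardiser of d is stated; dropping them is not needed.
- Carry forward to the later trial only the SD, pre/post correlation, adherence, missingness and attrition, each with a confidence interval. Take its target difference from a minimally important difference or from controlled data.

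The cost is wording and reporting on the same data, with no change to recruitment or data collection. The downside is a more modest claim for the study.

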## Introduction

Post-COVID-19 syndrome or Long COVID (LC) refers to persistent symptoms 12 weeks after SARS-COV2 infection and can include symptoms of physical fatigue, cognitive fatigue or ‘brain fog’, breathlessness, pain and psychological distress.^1–3^ An estimated 1.4 million people are reported to be affected by LC in the UK alone.^4^ The condition can be highly debilitating for some, particularly middle-aged individuals who were previously functioning at a high level and in demanding vocational roles.^5^ Many will experience significant disruption to employment, social and caregiving roles and participation in society.

Many LC symptoms such as palpitations, dizziness, fatigue, pain and breathlessness can be explained by the theory of dysautonomia.^6 7^ This is a state of episodic dysregulation in the autonomic nervous system (ANS) with sympathetic overdrive and reduced parasympathetic activity. Dysautonomia plays a significant role in the symptomology of many long-term conditions including multiple sclerosis, Parkinson’s disease, diabetes mellitus, fibromyalgia, chronic fatigue syndrome and migraine.^8^

One way of estimating and measuring autonomic function is through heart rate variability (HRV), as cardiac rate and rhythm are controlled largely by the ANS. The parasympathetic nervous system chiefly activates a slowing of heart rate through the vagus nerve, and the sympathetic response acts through the activation of β-adrenergic receptors.^9^ HRV can be measured either in the time domain or frequency domain. HRV represents a measure of the variation in time between heartbeats (captured on an Electrocardiogram (ECG) strip as a time interval between the R waves of the QRS complexes). A low HRV is associated with sympathetic nervous system activation, also described as a state of ‘fight or flight’. Higher HRV correspond with parasympathetic nervous system activation and is believed to reflect a state of rest and recovery. Lower HRV has been observed to be associated with fatigue and pain symptoms of chronic fatigue syndrome/myalgic encephalomyelitis and fibromyalgia^10–12^ as well as other chronic physical and mental health pathologies including asthma, anxiety and stress.^10–14^

### HRV biofeedback

When physiological parameters such as HRV are monitored in real time with self-regulation techniques such as breathing exercises applied to influence the parameters, this is known as biofeedback.^15 16^ In this study, for monitoring and modulating the HRV, we are using breathing techniques to encourage the predominance of parasympathetic nervous activity through vagus nerve activation. To the best of our knowledge, there have not yet been any studies of HRV biofeedback (HRV-B) in LC. However, HRV-B using breathing techniques has been tested in other clinical conditions such as asthma,^13^ depression^17^ and fibromyalgia.^12^ A normal respiratory rate is between 12 bpm and 20 bpm.^18^ The optimal breathing frequency to produce maximal increase in HRV varies for each individual but on average is between 5.5 bpm and 6 bpm and is known as resonant breathing.^13 18 19^ Resonant breathing helps to restore autonomic balance due to baroreflex gain and vagal activation.^13 18–20^

There are several means of assessing HRV but most commonly these include the use of either wearable devices such as smartwatches or chest straps, or through small attachable Holter ECG units. These are non-invasive and readily available, although reliability differs between devices and platforms. Many commercial HRV devices are associated with smartphone app technology, which can be readily downloaded and made available to participants for monitoring. Of the consumer grade devices available to monitor HRV the Polar H10 chest strap is felt to be the most reliable and remains accurate even during high-intensity activity.^21^ The Polar H10 can be linked with the Elite HRV app, which provides real-time feedback on HRV and the user’s response to breathing techniques. The combination of Polar H10 chest strap and Elite HRV app has been effectively used to harness real-time physiological data, for example, in athletes.^22^ In contrast, many wrist-worn devices such as Fitbit return a measure of HRV only while the user is asleep due to motion and other interference sources, meaning real-time HRV-B is not possible.

The aim of this study is to determine the feasibility and impact of a structured HRV-B regime incorporating diaphragmatic breathing exercise, on LC symptoms. We wish to test the acceptability and compliance of the intervention and estimate effect on symptoms using standardised validated measures of LC and dysautonomia.

### Aims and objectives

The aim of this study is: to assess the feasibility of a 4-week HRV-B-structured breathing programme in individuals with LC.

The objectives include:

Does breathing exercises through HRV-B increase HRV among participants with LC?Are consumer-grade monitors appropriate technology to use for HRV-B in the domiciliary setting?Does regular HRV-B have any effect on LC symptoms?

## Methods

### Study design

This is a phase 2 uncontrolled open-label feasibility study of a home technology-based HRV-B in 30 individuals with LC. Potential participants will be identified through the Leeds COVID-19 Rehabilitation Service, based at Leeds Community Healthcare NHS Trust. The study period will be 6 weeks for each participant. The study start date is 24 January 2022, and the anticipated end date is 31 March 2024.

### Eligibility criteria

The inclusion criteria are

Age ≥18 years.Confirmed LC diagnosis as per the National Institute for Health and Care Excellence (NICE) criteria for post-COVID syndrome.^1^Self-rating of at least ‘moderate’ or ’severe’ on dysautonomia questions of palpitations or dizziness on the COVID-19 Yorkshire Rehabilitation Scale (C19-YRSm).^23^Abnormal NASA Lean Test (NLT).^24–26^HR increase in 30 bpm or ≥120 bpm.Blood pressure (BP) decrease in 20 mm Hg systolic or 10 mm Hg diastolic in the first 3 min of standing.

NLT is an accepted measure of cardiovascular instability and is conducted at initial assessment clinic for all LC service users in the Leeds COVID-19 rehabilitation service. The patient lies down for 2–5 min prior to the test with HR and BP taken each minute to calculate average supine values. They then stand with heels 6 inches from a wall and lean back against it with HR and BP taken each minute for 10 min. Abnormal results (as described above) are demonstrated through orthostatic hypotension or tachycardia on standing which are hallmarks of dysautonomia and, therefore, objectively quantifiable. The participants who have dysautonomia symptoms but do not meet the mentioned thresholds will not be included in this feasibility study but will be potential recruits for future larger scale studies using the same intervention.

The exclusion criteria are

Unable to use the wearable or smartphone app technology.Cognitive difficulties or mental health disorders causing inability to consent.Any cardiac arrhythmias that are being planned for further investigations and specialist management in the Cardiology service.Any unstable cardiorespiratory disease that needs further medical interventions (except asthma management).

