### Post-HRV-B phase

The participant will be asked to stop the HRV-B intervention after completing 4 weeks of the treatment. They will be asked to continue using the Fitbit device for another week when not doing the intervention. They will then either be invited to a research clinic or be visited at home by a study researcher. At this appointment (A3), the participant will complete:

C19 YRSm: the C19-YRSm will be completed by the patient every week for a total of 6 weeks. There will be a total of 7 C19-YRS documents completed.Fitbit charge 5 device and the Fitbit smartphone application.NLT and aAP.COMPASS 31.WHODAS.EQ-5D-5L.

During the A3 appointment, the Polar H10 strap and the Fitbit device will be retrieved.

The participants will be invited to complete a further C19-YRS, by email or postal 4 weeks after completion aAP for 24 hours and to email or post the results to the study researcher.

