### Outcome measures

*The primary outcome measure* is the C19YRSm, a self-reported patient-reported outcome measure to assess LC symptom severity, functional disability and overall health status.

*Secondary outcome measures* include:

Heart rate measures from chest strap:

7-day average HRV score out of 100—quantified by the Elite HRV app via the root mean square of successive differences between normal heartbeats (rMSSD). A natural log (ln) is applied to this figure and then expanded to generate a 1 to 100 score.Mean R–R interval.Heart rate.rMSSD.SDNN (SD of Normal to Normal intervals).Total power.Low-frequency power (LF).High-frequency power (HF).LF:HF ratio.

Fitbit data:

Sleep staging data.Resting heart rate.Daily activity levels, for example, step count and exercise type and duration.

Patient-reported outcome measures:

NLT and aAP.COMPASS 31.WHODAS.EQ-5D-5L.

During our final interaction with participants in the study, we will ask them the following questions to assess the feasibility of the study:

‘How did you find using the technology?’‘How did you find the breathing intervention?’‘Have you noticed any change in your symptoms?’

Their opinions and suggestions will be recorded as quotes in their participant files. However, we are not planning to undertake a formal qualitative analysis of responses as it is not one of the main objectives of this study.

A summary of the schedule for the completion of outcome measures is shown in table 1.

**Table 1 T1:** Outcome measures summary schedule

	Initial assessment Clinic	Pre HRV-B phase (1 week)	HRV-B phase (4 weeks)	Post HRV-B phase (1 week)
Autonomic screening (NLT)	√			√
Autonomic function (COMPASS 31)		√		√
Home autonomic test (aAP)	√			√
Fitbit wrist strap HRV, sleep data		√	√ daily	√
Polar H10 chest strap HRV data			√ daily	
LC-specific PROM C19-YRSm		√	√ weekly	√
Daily function (WHODAS)		√		√
Quality of life (EQ5D-5L)		√		√

aAP, adapted Autonomic Profile; COMPASS 31, Composite Autonomic Symptom Score; C19-YRSm, modified COVID-19 Yorkshire Rehabilitation Scale; EQ-5D-5L, EuroQol 5-Dimension 5-Level; HRV-B, heart rate variability biofeedback; LC, long COVID; NLT, NASA Lean Test; WHODAS, WHO Disability Assessment Schedule.

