### Ethics and dissemination

The study has received ethical approval from Health Research Authority (HRA) Leicester South Research Ethics Committee (21/EM/0271). Informed consent will be obtained from all participants. Potential participants will have a minimum of 24 hours to review the PIS and discuss queries with the researcher prior to signing the written consent. General Data Protection Regulation (GDPR) rules will be strictly followed for all data gathered during the study. All data will be fully anonymised as soon as practical. All devices used are (Conformité Européenne (CE) marked and are being used for their intended purposes. There is potential for minor skin irritation from wearing the Fitbit and Polar H10 devices. This will be enquired about at each weekly telephone review.

For participants with cognitive fatigue or ‘brain fog’ relating to LC, the length of the appointments with the researcher (A1, A2 and A3) may be longer than normal. Supplementary written information will be provided, and if necessary, each of these appointments may be conducted in two shorter sessions to reduce information overload and possible impact on LC symptoms. Participants will be advised that they do not need to proceed with the appointments or the study if they do not want to. All appointments other than the initial NLT can occur at the participants’ homes to reduce travel and inconvenience. Participants are free to withdraw at any point in the study. They will be encouraged to give reasons for the withdrawal, but it will not be compulsory to give a reason for withdrawal.

Dissemination will include both academic publications and lay summaries in various formats. Academic outputs will include both medical and engineering literature. Policy impact will be aided by our strong existing links to NHS England and the UK Long COVID National Task Force. [name], who leads the NIHR project Long COVID Multidisciplinary consortium for Optimising Treatments and Services across the NHS (LOCOMOTION),^37^ is also an advisor for the WHO—Europe on COVID-19 rehabilitation and is also involved in the WHO working party developing a core set of outcome measures for LC.

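### The lean test used to select participants is also the only pre-intervention lean test, so the planned pre/post comparison on that outcome is biased towards improvement by regression to the mean

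*Protocol article*

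**What the plan says.** - **Entry.** Eligibility criteria requires an abnormal NLT. The heart-rate limb is "HR increase in 30 bpm or ≥120 bpm", and there is a blood-pressure limb of a 20 mm Hg systolic or 10 mm Hg diastolic fall. The section describes abnormality as orthostatic hypotension or tachycardia, so either limb appears to qualify. Symptomatic people below the thresholds are left out.
- **When the selecting test is done.** The same section says "NLT is an accepted measure of cardiovascular instability and is conducted at initial assessment clinic for all LC service users". Ethics and dissemination also refers to a single initial test: "All appointments other than the initial NLT can occur" at home.
- **Schedule.** In Table 1 the row "Autonomic screening (NLT") is ticked under the initial assessment clinic and the post-HRV-B phase only. The A1 baseline list (Pre-HRV-B phase) and the A2 list (HRV-B phase) contain no NLT. The A3 list does: "NLT and aAP.COMPASS 31.WHODAS.EQ-5D-5L".
- **Role.** Outcome measures lists the NLT among the secondary outcomes.
- **Analysis and design.** Statistical analysis plans paired t tests of pre/post differences with Bonferroni adjustment, plus Cohen's d and partial eta squared. Study design states: "This is a phase 2 uncontrolled open-label feasibility study of a home technology-based HRV-B in 30 individuals with LC".

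**The concern.** A group chosen because one noisy reading crossed a threshold will, on average, read closer to the clinic mean when measured again. This holds for any test-retest correlation below 1 and needs no treatment effect. A control arm would show the same drift and let it be subtracted, but this study has none. Bonferroni adjustment guards against many tests of true null hypotheses. It does not re-centre a comparison whose null expectation is not zero.

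The NLT matters because it is the one researcher-conducted physiological autonomic test with a value before and after the intervention. The chest strap has no pre-phase reading, COMPASS 31 is self-reported and the adapted Autonomic Profile (aAP) is self-measured. The abstract says the study will estimate efficacy, and the strengths and limitations box says that estimate will shape the size of a later controlled trial. A spurious NLT effect size could therefore be carried forward.

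The article does not state the interval between the clinic test and A1, so natural recovery may add to the shift.

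**Working it through.** The article gives no mean, SD or reliability for the NLT and no powered figure to reproduce (Sample size: "A formal sample size calculation is not required for a feasibility study"). The calculation below is therefore an illustration.

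**From the article:** n = 30; heart-rate threshold 30 bpm; systolic threshold 20 mm Hg; no control arm; paired t test.

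**Assumed:**
- heart-rate rise among clinic attendees: mean m = 22 or 28 bpm, SD s = 12 or 14;
- systolic fall: mean 5, SD 10 mm Hg, independent of heart rate;
- test-retest correlation r = 0.5 to 0.9;
- no treatment effect.

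The routes of heart rate ≥120 bpm and diastolic fall are left out for simplicity.

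**Expected null fall in heart-rate rise, entry by either limb.** With c = (30 − m)/s:
- pH = 1 − Φ(c);
- pB = 1 − Φ((20 − 5)/10) = 1 − Φ(1.5) = 0.0668;
- pS = 1 − (1 − pH)(1 − pB);
- fall = (1 − r) × s × φ(c) × (1 − pB) / pS.

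At r = 0.7:

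| m, s | c | φ(c) | pH | pS | fall (bpm) |
|---|---|---|---|---|---|
| 22, 12 | 0.667 | 0.3194 | 0.2525 | 0.302 | 0.3×12×0.3194×0.9332/0.302 = 3.5 |
| 22, 14 | 0.571 | 0.3388 | 0.2839 | 0.332 | 0.3×14×0.3388×0.9332/0.332 = 4.0 |
| 28, 12 | 0.167 | 0.3934 | 0.4338 | 0.472 | 0.3×12×0.3934×0.9332/0.472 = 2.8 |
| 28, 14 | 0.143 | 0.3949 | 0.4432 | 0.480 | 0.3×14×0.3949×0.9332/0.480 = 3.2 |

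**Simulation of the paired t test.** Test and retest values were drawn from a bivariate normal distribution, truncated by the entry rule and grouped into samples of 30. The simulated falls agree with the formula. The level 0.005 stands for Bonferroni with ten comparisons (0.05/10). Ten is an assumption, because the article does not give the number.

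| r | null fall (bpm) | false improvement at 0.05 (nominal 2.5%) | at 0.005 (nominal 0.25%) |
|---|---|---|---|
| 0.5 | 4.7–6.7 | 58–77% | 24–43% |
| 0.7 | 2.8–4.0 | 37–54% | 11–21% |
| 0.9 | 0.9–1.3 | 15–22% | 3–5% |

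At r = 0.7 the SD of the change is 9.0 to 10.5 bpm. The spurious paired Cohen's d is therefore about 0.31 (2.80/8.95) to 0.39 (3.52/9.07).

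**Sensitivity to the entry rule.** If everyone entered on heart-rate rise alone, fall = (1 − r) × s × φ(c)/pH, which is 3.3 to 5.0 bpm at r = 0.7. Entry through blood pressure dilutes the heart-rate artefact but does not remove it.

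**With a fresh baseline.** If a second pre-intervention NLT is the baseline and the clinic test serves only for selection, the expected null change is about 0 bpm and the two-sided error is about 5%. This was simulated with mean 25, SD 12, heart-rate entry, r = 0.5 to 0.9 and equal correlation between occasions.

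**The case against.** The strongest reply is that little hangs on the NLT. It is one of many secondary outcomes, the primary outcome is the C19-YRSm, the stated aim is feasibility, the Sample size section disclaims measuring an effect size, and no decision rule uses the NLT. The Statistical analysis section does not name the NLT as a tested variable. The aAP measures lying and standing heart rate and blood pressure against the same criteria and is not an entry test, so it is a less directly selected comparator. These points lower the severity. They do not remove the bias, because nothing exempts the NLT from the pre/post tests. The aAP is also unsupervised, and its baseline is placed at A1 in the text but at the initial clinic in Table 1.

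It may also be said that a journal article leaves detail to the full protocol. That is fair for the clinic-to-A1 interval. It does not answer the main point, because the printed schedule shows no second pre-intervention NLT and no analysis plan can supply a measurement that was not taken.

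Three stronger readings are tempting, and the article does not support them:
- **That the NLT result can only move one way.** This would be true of a count of abnormal results turning normal, which the article does not plan. Continuous values can rise: in the r = 0.7 illustration about 35% to 38% of participants have a larger heart-rate rise at retest.
- **That the C19-YRSm has the same fault.** Entry does use a rating "on dysautonomia questions of palpitations or dizziness on the COVID-19 Yorkshire Rehabilitation Scale". However, the scale is on the A1 baseline list, and Table 1 ticks it in the pre-HRV-B phase and not at the initial clinic. A separate baseline is therefore already scheduled.
- **That A3 will be in a different setting.** Post-HRV-B phase and Ethics and dissemination allow a home visit, while Equipment and technology speaks of conducting the NLT in clinic. The setting is unclear, not shown to differ.

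**Conclusion.** The point stands for the NLT alone. The selecting test is the only pre-intervention value, so a paired test or effect size on the NLT does not have a null expectation of zero. The direction is certain in expectation for any correlation below 1, and the effect falls mainly on the component by which a participant qualified. In one sample of 30 with a highly repeatable test, the shift could be small and not significant.

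The size rests wholly on assumed inputs. At r = 0.7 the false-improvement rate is many times nominal, with or without Bonferroni adjustment. At r = 0.9 and level 0.005 it is 3% to 5%, still above the nominal 0.25%. Severity is moderate: the bias does not touch the primary outcome or the feasibility aim, but it changes what can be concluded from the NLT.

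**What to change.** **At no cost.** State that the screening NLT is an eligibility measure and will not be the baseline in a paired test, Cohen's d or partial eta squared. Report A3 values descriptively, with a sentence on regression to the mean, and claim no normalised proportion. In the r = 0.7 illustration about 28% to 39% of participants would no longer meet the simulated entry rule at retest with no treatment effect.

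**If an efficacy comparison on the NLT is wanted.** Record an NLT at the existing A1 or A2 visit, name it as the analysis baseline, and do the A3 test in the same setting. By the article's description the test takes 2–5 minutes lying plus 10 minutes standing, so 12 to 15 minutes at one visit. It also brings some orthostatic symptom burden. The blood pressure monitor is already in use in the study.
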